#### Main outcome measure

In the present study cardio-metabolic risk factors were calculated by integrating objective measurements of BMI, waist circumference, muscle mass, percentage fat, endurance test, total serum cholesterol, HDL, non-HDL, mCRP and HbA1c. Firstly, all variables were divided into quartiles. Secondly, the results were dictomised as the children in the quartile of highest risk factor were given the score 1, and the children in the other quartiles were scored 0. Thirdly, children categorise with risk factors were assigned to one of 11 risk factor categories, 0–10, depending on their number of risk factors. Fourthly, the probability of children having 0 to 10 risk factors were calculated using the binominal probability formula (*n*! • *p*
^r^ • (1 – *p*)^*n-r*^ / (*r*! • (*n*-*r*)!) [49]. Where *n* is the possible number of risk factors (total of 11), *p* is the probability of having a risk factor (highest risk factor quartile: 0.25) and *r* is the number of risk factors for which the probability is calculated (0–10) [17]. Fifthly, the observed number of children in each group was compared to the expected number by calculating the ratio and plotting with a 95% confidence interval. Finally, a composite cardio-metabolic risk factor profile was calculated using Z-scores by age and gender for selected risk factors. The Z-scores were then summed for each individual regarding the individual risk factors to create the clustered risk score [17].

The occurrence of cardio-metabolic risk factors in the HOPP study was calculated at baseline. In addition, the calculus is to be computed annually to reveal any change in cardio-metabolic risk factors as a result of the intervention.

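### The annual observed/expected risk-count ratio measures clustering of risk factors within a child, not the programme effect it is said to reveal

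*Protocol article*

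**What the plan says.** The Main outcome measure section of the Protocol article (under Analytic possibilities) builds the outcome from ten variables: "BMI, waist circumference, muscle mass, percentage fat, endurance test, total serum cholesterol, HDL, non-HDL, mCRP and HbA1c". Each is cut at its quartiles and scored 1 in the highest-risk quartile and 0 otherwise, and children are "assigned to one of 11 risk factor categories, 0–10, depending on their number of risk factors". Then "the probability of children having 0 to 10 risk factors were calculated using the binominal probability formula", with n set to 11 and p to 0.25. Next, "the observed number of children in each group was compared to the expected number by calculating the ratio", shown by "plotting with a 95% confidence interval". Group here means a risk-count category, not intervention or control schools. The last step is a summed Z-score by age and gender. A separate closing paragraph says that, beyond the baseline calculation, "the calculus is to be computed annually to reveal any change in cardio-metabolic risk factors as a result of the intervention".

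Two later sections bear on this. Analyses of effect foresees a 2015 to 2016 comparison covering both intervention and control schools. Analyses of longitudinal effect mentions a yearly comparison of the two sets of schools, and a mixed model for the main outcome with school group as a fixed factor.

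**The concern.** The closing paragraph gives the whole calculation, including the observed/expected ratio, the job of showing what the intervention did. The ratio cannot do that job. Its reference distribution assumes that every risk flag is independent of every other, and nothing in it refers to school group, to the child's baseline or to calendar year. It answers whether risk factors cluster within children, which is to be expected with or without a programme.

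At stake is how the main-outcome display is read. An excess of children with many risk factors, with an interval well away from 1, would be expected in the control schools too. If the programme worked and the quartile cuts were held at baseline, the high-count ratio would fall towards or even below 1 while the zero-count ratio moved further above 1. Distance from 1 is therefore not a measure of benefit or harm, and a change between years within one arm mixes a change in clustering with a change in risk level.

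**Working it through.** **Inputs.** From the protocol: ten listed variables; p = 0.25; stated n = 11; 1344 children with blood samples (Blood samples section), the most who could have every factor; 1545 of 2297 children in intervention schools (Table 1). Not given, so assumed below: the correlations between factors, the type of confidence interval, and the split of blood samples by arm.

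**The plan's own expectation.** E_r = N × C(n, r) × 0.25^r × 0.75^(n−r). With N = 1344 and r = 0, n = 11 gives 1344 × 0.0422 = 56.8 and n = 10 gives 1344 × 0.0563 = 75.7. The stated 11 does not match the ten variables listed there (the Abstract reaches eleven by adding PA level). With ten independent factors that mismatch alone would put the zero-count ratio at 75.7 / 56.8 = 1.33. It is a separate matter, and n = 10 is used from here on so that it plays no part.

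**What a ratio of 1 means.** If each factor is cut at the sample's own quartile, the mean count is 10 × 0.25 = 2.5 whatever the dependence. The variance is 10 × 0.25 × 0.75 = 1.875 under independence, and 1.875 plus twice the sum of the pairwise covariances otherwise. Net positive covariance puts more children than the binomial at both ends and fewer in between.

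**Dependence visible in the document.** The Blood samples section computes non-HDL as serum cholesterol minus HDL, and all three are scored. High cholesterol and low HDL both raise non-HDL. BMI, waist and percent fat all reflect adiposity.

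**Simulation with no programme effect.** Ten factors, N = 1344, exact Poisson 95% intervals. Muscle mass and HbA1c are taken as independent of the rest; lipid SDs are assumed to be 0.7 (total cholesterol) and 0.33 (HDL). Lipid only: the sole link is the non-HDL identity, with total cholesterol and HDL uncorrelated. Adiposity 0.5 and 0.7: BMI, waist and percent fat mutually correlated at that value; adiposity with endurance, mCRP and HDL at 0.15 or 0.3 in absolute value; total cholesterol with HDL at 0.2. Cells give observed/expected and, in brackets, the share of runs whose interval excludes 1.

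| Count | Independent | Lipid only | Adiposity 0.5 | Adiposity 0.7 |
|---|---|---|---|---|
| 0 | (2.5%) | 1.32 (78%) | 1.90 (100%) | 2.33 (100%) |
| 1 | (0.7%) | 1.07 (11%) | 1.09 (20%) | 1.13 (56%) |
| 4 | (2.1%) | 0.98 (2%) | 0.92 (14%) | 0.83 (69%) |
| 6 | (2.1%) | 1.47 (62%) | 2.17 (99.6%) | 2.71 (100%) |
| 7 | (3.3%) | 2.02 (26%) | 4.17 (98%) | 6.48 (100%) |

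The variance of the count rises from 1.875 to 2.24, 2.83 and 3.36 across the columns. If total cholesterol and HDL correlate at 0.3, the lipid-only exclusion rates fall to 45%, 24% and 7% at counts 0, 6 and 7.

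**Both arms.** Splitting blood samples in proportion to enrolment gives 1344 × 1545 / 2297 ≈ 904 intervention and 440 control children. In nine-factor versions with no effect, the ratios were about 1.7 to 2.8 for zero and for five or more factors, and the interval excluded 1 in 96–100% of runs in both arms; counts 1 and 4 did so in only 6–30%. Another assumed set gave 100% in both arms. With its correlations halved, it gave 99% and 99.7% (zero; five or more) with 904 children, and 84% and 90% with 440.

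**Under a benefit.** With a 0.2 SD improvement in every factor and cuts fixed at baseline, the five-or-more ratio fell from 2.7 to 1.5 (halved correlations: 1.8 to 0.86), and the zero-count ratio moved further from 1. If quartiles are instead re-cut each year, an improvement shared equally by all children in the sample left every child's count unchanged.

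**Between arms.** (O_I / (N_I × π_r)) / (O_C / (N_C × π_r)) = (O_I / N_I) / (O_C / N_C), where π_r is the binomial probability of count r. The binomial cancels. Comparing the ratio between arms rejected in 4–6% of no-effect runs, with pupils treated as independent.

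**The case against.** A reader might infer that the trial will declare an effect whenever the interval excludes 1, and so has a false-positive rate near 100%. The document does not support that. It says the ratio is calculated and plotted; it sets no decision rule, and the stated annual aim is to show change, not distance from 1. The exclusion rates above describe the reference value, not the error rate of a planned test.

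Nor can one say that the main outcome lacks a usable effect analysis. The annual calculation also covers the summed Z-score, and Analyses of effect and Analyses of longitudinal effect both foresee comparing intervention with control schools, the latter naming the main outcome. The ratio does no harm when contrasted between arms, since the binomial drops out. Not every category departs from 1 either: counts around 1 and 4, where the observed and expected curves cross, often cover it. All of this stands and narrows the point.

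It does not remove it. The closing sentence links the annual calculation to the intervention without naming a control comparison, and the binomial steps are part of that calculation. The mixed model is described as something the design permits, whereas the annual calculation is stated as something that will be done.

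**Conclusion.** Wrong as written, in a limited sense: the observed/expected ratio is included in a calculation meant to show an intervention result, yet its null value means independent risk factors, not absence of a programme effect. Departures at the lowest and highest counts are expected in both arms with no effect, at roughly 1.7 to 2.8 under the assumed correlations, with intervals excluding 1 in most to all runs. These sizes rest on correlations, interval type and arm split that the protocol does not give, and on treating muscle mass as unrelated to adiposity in the ten-factor runs. That the binomial contains neither arm nor time, and that the lipid factors are linked by definition, rests on no such assumption. The Z-score and the planned comparisons between schools are not affected.

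**What to change.** In Main outcome measure, state that the observed/expected binomial ratio describes clustering of risk factors only. Replace the closing sentence about the intervention with the intervention-versus-control comparison of the risk-factor count and the summed Z-score, adjusted for the child's own baseline value and accounting for school, through the mixed model already outlined in Analyses of longitudinal effect. Fix the quartile cuts and Z-score references at baseline so that a shared improvement is not removed by re-cutting. If the category plot is kept at follow-up, use the control schools' distribution in the same year as its reference, with each arm's baseline distribution alongside.

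The cost is wording and a little extra analysis on data already being collected, with no new participants. Intervals will be wider than those on the ratio plot once school is accounted for. Because the children grow, the fixed cuts need to be specific to age and gender; the baseline sample stops at 6th grade, so the reference for 7th grade has to be specified.

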##### 6) Blood samples

Blood samples are to be taken annually. However, not all children comply with this procedure. The children were given an opportunity to opt out on the blood sample test, while participating in the other test procedures. Hence, 58.4% (*n* = 1344) of the children completed blood sample procedures in a non-fasting state between 08.00 am and 13.30 pm at baseline. A similar number are expected in 2016.

Groups of four pupils were summoned from the classroom, making sure they had not performed strenuous exercise prior to sample collection. A phlebotomist collected samples in 4 mL tubes (Vacuette® Z Serum Sep Clot Activator and K2E K2EDTA) from the antecubital vein. The gel tubes were end turned and set to 30 min of coagulation before centrifuged at 2000 G for 10 min. Samples were transported to the laboratory and analyzed according to standard procedures. The executive laboratory at Vestfold Hospital Trust is certified according to NS-EN ISO 15189.

Samples were analysed for constituents related to physical capacity, dietary status, cardiovascular risk and inflammation. Ferritin, cobalamin (total vitamin B12) and holotranscobalamin (active vitamin B12) were measured on Architect i2000SR (Abbott Diagnostics, USA) with reagents from the supplier. Total cholesterol, HDL-cholestrol, iron and creatinine were measured on Vitros 5600 or Vitros 5.1 (Ortho-Clinical Diagnostics, USA) with reagents from the supplier. Micro C-reactive protein (mCRP) was measured on Vitros 5600 with reagents from Abbott Diagnostics. Blood counts were measured on Sysmex XE 2100 or XE 5000 (Sysmex, Europe) with reagents from the supplier. Hemoglobin A (HbA1c) test was measured on Tosoh G8 (Tosoh, Japan) with reagents from the supplier.

Blood samples were not taken fasting; hence triglycerides were not sampled. We were therefore not able to use Friedmans formula for estimating Low-density Lipoprotein Cholesterol (LDL-C). As a substitute non HDL-C were used (Serum cholesterol – HDL = non HDL-C) [26].

Any result outside the normal range, according to the laboratory at Vestfold Hospital Trust reference material used in the outpatient clinic, was reported to the team physician. He again contacted the parents to give appropriate advice, usually a follow-up at the child’s general practitioner.

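### Observed/expected ratios at risk counts 9 and 10, and at count 8 late in follow-up, are too sparse to show yearly or between-arm change

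*Protocol article*

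**What the plan says.** In the protocol article, the section Main outcome measure builds the risk count from "BMI, waist circumference, muscle mass, percentage fat, endurance test, total serum cholesterol, HDL, non-HDL, mCRP and HbA1c". That is ten variables. Each is dichotomised at its worst quartile, and children are "assigned to one of 11 risk factor categories, 0–10, depending on their number of risk factors". The expected distribution is binomial. Its p "is the probability of having a risk factor (highest risk factor quartile: 0.25", and its n "is the possible number of risk factors (total of 11", which does not match the ten variables listed. Then "the observed number of children in each group was compared to the expected number by calculating the ratio and plotting with a 95% confidence interval". The section closes by stating that "the calculus is to be computed annually to reveal any change in cardio-metabolic risk factors as a result of the intervention".

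Two other forms of the main outcome appear. In the same section, "a composite cardio-metabolic risk factor profile was calculated using Z-scores by age and gender for selected risk factors", and these scores are summed. The section Analyses of longitudinal effect offers a linear mixed model for the main outcome.

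The section on blood samples reports that 1344 children, printed as 58.4%, "of the children completed blood sample procedures in a non-fasting state between 08.00 am and 13.30 pm at baseline". The section Outcome measures says that the sample shrinks each year as the oldest grade leaves.

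**The concern.** The eleven counts are kept apart, and no pooling or minimum size is given for the upper ones. With p = 0.25 the binomial puts almost no probability on the highest counts, so the ratio there has a denominator of a small fraction of a child and a numerator of zero to a few children.

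The upper counts are where a reader would look for clustering of risk. If the same plot is redrawn each year, or drawn for each arm, one child entering or leaving a cell could look like a large worsening or improvement when nothing has changed.

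**Working it through.** **Inputs from the protocol article.** Ten listed variables, n printed as 11, and p = 0.25 (Main outcome measure). Blood in 1344 children at baseline (Blood samples). Sample of 2297, with 1545 intervention and 752 control; first grade 351, of whom 103 control (Table 1). Five of the ten variables need blood (total cholesterol, HDL, non-HDL, mCRP, HbA1c), so 1344 is the ceiling for a complete count. The article prints no expected numbers, so there is no stated figure to reproduce.

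**Expected numbers.** E(r) = N × C(n, r) × 0.25^r × 0.75^(n−r). One extra child moves the ratio by 1/E(r).

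| N = 1344 | E, n = 10 | 1/E | E, n = 11 | 1/E |
|---|---|---|---|---|
| count 7 | 4.15 | 0.24 | 8.57 | 0.12 |
| count 8 | 0.52 | 1.9 | 1.43 | 0.70 |
| count 9 | 0.038 | 26 | 0.16 | 6.3 |
| count 10 | 0.0013 | 780 | 0.011 | 95 |

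At counts 9 and 10 the expected number stays far below one even if all 2297 children had blood (n = 10: 0.066 and 0.0022; n = 11: 0.27 and 0.018).

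**By arm (assumption: blood samples split pro rata).** 1344 × 1545/2297 ≈ 904 and 1344 × 752/2297 ≈ 440. Count 8 then has E = 0.35 and 0.17 with n = 10, or 0.96 and 0.47 with n = 11.

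**In 2021 (assumption: 1344/2297 = 58.5% blood participation persists, no dropout).** 351 × 0.585 ≈ 205 children. Count 8 has E = 0.08 (n = 10) or 0.22 (n = 11). Count 9 has 0.006 or 0.024.

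**Spread with no true change.** A small E is not in itself imprecision: E is a constant, and precision depends on how many children are observed. Correlated factors put more children in the upper counts than the binomial predicts, so this was simulated. Ten Gaussian scores were cut at the upper quartile, with assumed correlations of 0.8 within adiposity (BMI, waist, percent fat), 0.5 within lipids and 0.1 elsewhere. Ratios use n = 10; ranges are 95%.

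- Count 7, N = 1344: about 29 children observed.
- Count 8, N = 1344: about 12 children, ratio roughly 10 to 38. At N = 205: about 2 children, range 0 to 5.
- Count 9, N = 1344: about 3.6 children. The upper limit is 8 children, 8/0.0385 = 208. The lower limit is zero or one child (ratio 0 or 26), because the chance of no child is about exp(−3.6) = 2.7%, right at the 2.5% point. At N = 205: 0 to 2 children, ratio 0 to 341.
- Five or more: 1.8 to 2.3 at N = 1344, and 1.4 to 2.7 at N = 205.

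With the other correlations at 0.2, the count-9 range at N = 1344 becomes about 104 to 390, still nearly fourfold.

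**Pooled category, n = 10.** P(5 or more) = 0.0781. Expected: 1344 × 0.0781 = 105; 440 × 0.0781 = 34; 205 × 0.0781 = 16. For 2021 controls, 103 × 0.585 ≈ 60 children and 60 × 0.0781 ≈ 4.7.

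**The case against.** The strongest reply is that the ratio is one descriptive step, drawn with a 95% interval that shows its own imprecision. The section ends with a summed Z-score, a mixed model is offered for the main outcome, and no test or decision is tied to a count-9 or count-10 ratio. Pooling and interval type are also details that a condensed article may leave to an analysis plan. Most of this stands, and it limits the weight of the point. Two things remain. The article does fix eleven separate categories and assigns the annual repetition the task of showing an intervention effect. And the interval is only a partial safeguard: one child at count 10 gives a ratio of 780 with an exact Poisson interval of about 20 to 4347 (n = 10), or 95 with 2.4 to 527 (n = 11). Both exclude 1.

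A reader might infer that counts 8 to 10 all expect less than one child and that one or two children move every one of these ratios by tens to thousands. The article does not support that. With the printed n = 11, count 8 expects 1.43 children in the whole baseline sample, and two children move its ratio by 1.4 (3.9 with n = 10). At n = 11, two children move even count 10 by only about 189. Under the assumed correlations count 8 holds about 12 children at baseline, so one child changes its ratio by about a twelfth.

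A reader might also infer that the sample cannot tell five risk factors from eight. At baseline it can: the simulated count-5 ratio is about 1.3, well clear of the count-8 range.

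**Conclusion.** The concern holds in a limited form. At counts 9 and 10 the expected number is far below one child under either n, and these ratios rest on zero to a few children from the start. Count 8 joins them late in follow-up and is thin when split by arm. Yearly or between-arm movement in these ratios carries almost no information about the intervention.

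The expected numbers follow directly from the article's own formula. The by-arm figures assume a pro rata blood split, and the 2021 figures assume constant blood participation and no dropout. The simulated ranges depend on assumed correlations, and the article gives none. The article also does not say how the arms enter the ratio; a split is assumed here because an intervention effect needs one.

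It would go too far to say that the main outcome fails. The summed Z-score and the mixed model do not use these cells.

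**What to change.** 1. Reconcile ten listed variables with n = 11 first, since this changes every expected number (by a factor of 8.25 at count 10).
2. For the annual and between-arm comparison, replace the separate upper counts by one pooled category with the same cut in all years and both arms. Five or more is one choice, with expected numbers of about 105 at baseline, 34 in controls at baseline and 16 in 2021 with both arms together (n = 10). State exact Poisson intervals.
3. For counts 9 and 10, and for count 8 late in follow-up, give observed and expected numbers and do not interpret a ratio.
4. Do not add a rule that hides every cell with an expected number below 5. It would remove count 7 at baseline (expected 4.2, about 29 observed in simulation) and the pooled category in 2021 controls (expected about 4.7).

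The cost is a few sentences and one recoding step. The pooled comparison loses the gradation between five and eight factors, which is visible at baseline, so the separate counts can stay as a baseline description.

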#### Baseline analyses

Baseline tests allows for cross sectional analyses for all variables. The large sample permits establishing representative normal materials for selected variables for each age group and gender. Inference between related variables may disclose health related correlations. Comparison with existing representative normal materials may document any changes regarding health related issues, for example an increase or decrease of overweight in the Norwegian child population.

Based on the cross-sectional data generated at baseline, the large sample size permits establishing normal materials in a variety of variables. In addition, multiple regression models were used to analyse inference between variables.

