In 2014, politicians in Horten municipality, Norway, initiated a health promotion program for children called the Health Oriented Pedagogical Project (HOPP). HOPP was initiated in response to an increasing prevalence of obesity, inactivity and lifestyle related diseases in the local child population. The main objective is to evaluate the effects of a school-based PA intervention program on cardio-metabolic risk, offering a proxy for later non-communicable disease. Secondary objectives include assessment of physical, psychological and academic performance variables (Fig. 1).

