## Methods/design

### Study population and inclusion criteria

The HOPP study is a controlled longitudinal school-based PA intervention. Seven elementary schools in Horten municipality, Vestfold County, Norway are intervention schools. Two control schools in Akershus County, Eiksmarka school (*n* = 520) and Rasta school (*n* = 465), were included. The control schools were recruited based on estimated socioeconomic level, using a centralised Norwegian program for systematic quality work in schools and kindergartens called PULS. This represent a total population of 2817 pupils of which 1815 children received the intervention as a part of the pedagogical platform in Horten municipality. All children were invited to be part of the research project. Based on recruitment procedures a total baseline participation of 2297 pupils (82%) was achieved. The children were recruited from 1^st^ - 6^th^ grade (age 6–11 yrs) (Table 1).

**Table 1 Tab1:** Baseline population for all grades as of 2015 is shown, as well as the sample size, based on children whose parents gave consent to participation in the research project

Grades	1	2	3	4	5	6	Total
Population	457	484	457	462	461	496	2817
Sample	351	381	370	389	381	425	2297
Intervention schools	248	264	229	264	269	271	1545
Control schools	103	117	141	125	112	154	752

The sample size is divided into intervention and control schools

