### Limitations of the study

One challenge with all longitudinal designs, is dropout as the participants decline completing the intervention or do not show to tests. In addition to regular dropouts, the HOPP study has a decreasing number of participants as the children are transferred to junior high school. This design have two major implications: ^1)^ the amount of years the pupils are in the intervention varies depending on the age at inclusion. Children born in 2003 only participate one year before exit. Those born 2004 are enrolled in two years, born 2005 in three years, and so forth. This implies challenges regarding the statistical analyses, as results from pupils with fewer years in intervention must be weighted less than pupils with additional years. ^2)^ Due to age-specific tests not all children receive all tests. In those tests only a limited amount of participants are to be analysed in an effect of intervention. Instead secular trends are to be used.

A major challenge in all interventions is compliance, and in the present study the teacher’s compliance is essential. Encouraging teacher’s to complete the intervention every day is a major challenge, and is taken care of by Horten municipality. Two designated teachers at each school as well as a centralised coordinator, performed daily encouragements as well as written control of participation. The individual compliance of each pupil is more difficult to survey. The participation rate as being part of the class is registered using reports of absence from school. However, in what extent and what intensity each pupil performed each task are more difficult to control.

Due to Horten municipality decision on giving all schools in the municipality the same school-based PA program, a randomised controlled trial was not possible. However, using control schools with corresponding socioeconomic status, a controlled design was used.

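### Baseline norms are called representative because the sample is large, and may be read as national change, but the sample is one municipality plus two recruited schools

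*Protocol article*

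**What the plan says.** The claim is in the protocol article under Analytic possibilities, Baseline analyses: "The large sample permits establishing representative normal materials for selected variables for each age group and gender". The second paragraph of that section repeats the argument from size. Between the two, the section says that comparison with existing norms may document changes in health, "for example an increase or decrease of overweight in the Norwegian child population".

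The sampling is described elsewhere in the article:

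- **Study population and inclusion criteria, intervention schools:** "Seven elementary schools in Horten municipality, Vestfold County, Norway are intervention schools".
- **Background, origin of the project:** local politicians began it in 2014, and "HOPP was initiated in response to an increasing prevalence of obesity, inactivity and lifestyle related diseases in the local child population".
- **Study population and inclusion criteria, control schools:** "Two control schools in Akershus County" were added, and "The control schools were recruited based on estimated socioeconomic level". Limitations of the study describes the result as "using control schools with corresponding socioeconomic status, a controlled design was used".
- **Blood samples:** children could opt out. "Hence, 58.4% (*n* = 1344) of the children completed blood sample procedures".

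Limitations of the study covers dropout, age-specific tests, compliance and the lack of randomisation. It does not discuss whether the children represent any wider population.

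**The concern.** Two inferences are made, and neither follows from what precedes it.

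The first runs from a large sample to representative norms. A large sample narrows the confidence interval around whatever the sampled children have in common. It does not bring those children closer to a population from which they were not drawn.

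The second runs from a gap between this sample and existing norms to a change in Norwegian children. The two sets of data differ in place as well as in time, and the section describes no way of separating the two. A stable difference between these schools and the country would look the same as a national trend.

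At stake are the normative tables by age and gender and any published statement about national overweight based on them. If such tables are later used as reference values, the label matters more than the precision.

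**Working it through.** **Inputs (Protocol article).** Study population and Table 1: population 2817, of which 1815 in the intervention municipality; sample 2297, with 1545 intervention and 752 control; control school sizes 520 and 465. Blood samples: 1344 children.

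**Reproducing the stated figures.** Overall participation is 2297/2817 = 81.5%, stated as 82%. Table 1 sums correctly (2817, 2297, 1545, 752). Blood sampling is 1344/2297 = 58.5%, stated as 58.4%, a rounding difference.

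**Where the sample comes from.**

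- Intervention municipality: 1545/2297 = 67.3%.
- Two control schools: 752/2297 = 32.7%.

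No random or nationally stratified draw is described for either part.

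**Participation by group.**

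- Intervention: 1545/1815 = 85.1%.
- Control: 752/(520 + 465) = 752/985 = 76.3%, or 752/(2817 - 1815) = 752/1002 = 75.0%. The two denominators differ because 1815 + 520 + 465 = 2800, not 2817. This makes no difference here.

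**Blood variables.** 1344/2817 = 47.7% of all pupils. Spread over six grades and two sexes, that averages 1344/12 = 112 children per cell.

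**What size does to the second inference (illustration on assumed values).** The documents give neither a prevalence nor a local offset. Let p be the true prevalence and b a fixed difference, in either direction, between these schools and the country, with no change over time. Treating children as independent, SE = √(p(1 - p)/2297). The chance that a two-sided 5% test against a fixed national value reports a change is Φ(-1.96 - b/SE) + 1 - Φ(1.96 - b/SE).

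| Assumed p | SE (points) | b = 1 point | b = 2 points | b = 3 points |
|---|---|---|---|---|
| 15% | 0.75 | 27% | 77% | 98% |
| 20% | 0.83 | 22% | 67% | 95% |

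An SE that allowed for clustering in nine schools would be larger and these chances lower. The direction of the argument is unchanged: b/SE grows with the square root of n, so for any fixed non-zero offset a larger sample makes a false report of change more likely. With b = 0 the chance is 5%. The table shows sensitivity to an unknown and does not estimate what happened.

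**The case against.** The other side has several fair points.

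- **Local coverage is good.** All children were invited, elementary school is compulsory, and 82% took part. This stands, but it supports describing these nine schools, not Norway.
- **The text is hedged.** The section sits under a heading about possibilities, speaks of selected variables, and says only that comparison may document change. The sentence claiming representativeness names no target population; the national population appears in a later sentence. This stands in part. The hedge softens the trend statement, but the claim of representativeness still rests on size alone, and the only population the section names as a target of inference is the national one.
- **Norms are a side product.** They are neither the main nor a secondary objective. This stands and limits the severity.

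Stronger readings are tempting, and the documents do not support them.

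- **That the area was selected for obesity, so the norms are shifted towards higher risk.** The investigators did not sample the municipality on obesity; it started the programme itself. Background reports a rising local prevalence, not a level above the national one, and also reports increasing adiposity in Norway generally. No local excess is shown.
- **That the participation figures reveal a bias in a known direction.** They show that non-participation existed and differed by group. Nothing says how non-participants differed, and their absence could push values either way.
- **That the controls were matched on risk.** They were recruited at school level on socioeconomic level, which is neither individual matching nor selection on adiposity.
- **That the effect estimate is compromised.** This point concerns the baseline normative analyses and leaves the comparison of intervention with control schools as it is.

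**Conclusion.** The point holds in a limited form and is minor. The Baseline analyses section draws representativeness from sample size and allows a difference from existing norms to be read as change in Norwegian children. The article's own account of recruitment supports neither.

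This is a stated inference that does not follow, so a fuller protocol or analysis plan that merely added detail would not cure it. The conclusion rests only on the described sampling and on the fact that a comparison across place and time cannot by itself separate the two.

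The size and direction of any bias cannot be known from the documents. The offsets in the illustration are assumptions, and a true offset of zero is not excluded. The primary outcome, the sample size and the between-group analyses are not touched.

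**What to change.** In Baseline analyses:

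1. Delete the word representative, and call the tables reference values for the participating schools, in both places where the section argues from sample size.
2. Replace the sentence on national change. A difference from existing norms is to be reported as a difference between samples, not as a change in the Norwegian child population.
3. For blood variables, label the values as coming from children who volunteered. Compare BMI, waist circumference and endurance test results between those who gave blood and those who did not. Anthropometry and the endurance test are scheduled for all grades in Table 2, so no new data are needed.

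The cost is a few words and one descriptive table. The downside is a less far-reaching secondary claim.
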